## Methods

### Study design and cohort

This is a multi-center, blinded, prospective, longitudinal, observational study to evaluate phosphorylated alpha synuclein pathology in cutaneous tissues in individuals with prodromal disease (iRBD) and PD across a range of disease (Hoehn and Yahr stage I, II & III). This study aims to enroll 75 subjects diagnosed with PD with 25 subjects enrolled in each Hoehn and Yahr stage (I, II, and III), totaling 75 participants (16). Their disease state will be assessed by the International Parkinson and Movement Disorders Society Unified Parkinson’s disease rating scale (MDS-UPDRS) completed at the baseline visit. Additionally, 25 subjects diagnosed with iRBD, confirmed by polysomnogram (PSG), without evidence of PD, will be included based on their medical history. A total of 100 subjects will be enrolled. Subjects will be evaluated at baseline, 6 months, 12 months, and 18 months (+/− 30-day window).

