c One 4 mL EDTA tube for genetic testing for inherited forms of PD (LRRK2, GBA1, PRKN, PINK1, and SNCA) which is collected at the baseline visit only.d One 10 mL EDTA tube collected at all visits for blood-based biomarkers (plasma p-tau-217, neurofilament light chain, glial fibrillary acidic protein). as exploratory outcomes.

8 Three millimeter diameter and 3–4 millimeter depth punch skin biopsies taken from the posterior cervical area 3 cm lateral to the C-7 spinous process, distal thigh 10 cm above the lateral knee, and distal leg 10 cm above the lateral malleolus after local analgesia with 1% lidocaine (9).9 Cognitive/Neurological Testing and Questionnaires: All participants will complete the following questionnaires/assessments:

e European Quality of Life Instrument (EQ-5D & VAS) (20)f SLUMS cognitive assessmentg Parkinson’s Disease Questionnaire-39 (PDQ-39) (21)h Orthostatic Hypotension Questionnaire (OHQ) (22)i REM sleep behavior disorder questionnaire (RBDSQ)j Scales for Outcomes in Parkinson’s Disease-Autonomic (SCOPA-AUT)k Geriatric Depression Scale-short form (GDS)

10 Collection of medical records for the last 3 years including any imaging (DaTscan, MRI, PET, SPECT, neurologic testing or genetic testing)

All assessments and blood collection will be repeated once every 6 months, with the exception of genetic testing which takes place only once at the baseline visit.

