#### Statistical considerations

Descriptive statistics will be used to report all demographic information and clinical examination findings for all groups (PD stages I-III and iRBD). For continuous variables data will be reported as mean, standard deviation, median, minimum, maximum and inter-quartile range.

For the primary objectives, the presence or absence of P-SYN will be reported as a binary outcome for the first objective (detection of P-SYN). Quantitation of P-SYN will be measured as a continuous variable for the second objective (quantitation of P-SYN). We have established that a P-SYN > 0 is defined as a ‘P-SYN positive’ result and will separate groups using dichotomous measures. We will also investigate ROC curve analysis to determine if an alternative value would maximize sensitivity and specificity using continuous quantitative measurement of P-SYN. For comparisons over time, the initial biopsy results will be compared against future biopsy results using Krippendorff’s alpha reliability estimate. Reliability will be measured by quantified continuous P-SYN values between visits with the change in continuous values used to determine mean change over time. Additional endpoints will include change in disease severity over time, or phenoconversion to clinically apparent synucleinopathy (in patients with iRBD).

Data will be compared first using repeated measures Analysis of Covariance (ANCOVA), with phenoconversion/disease progression as the predictor variable. The primary dependent variable is the quantitative measure of P-SYN deposition. Other key covariates will include sex, cognitive examination scores, disease duration, UPDRS Part 2 and Part 3 total scores, and autonomic nerve fiber density (pilomotor nerve fiber density and sudomotor nerve fiber density) (32). These will be evaluated individually and together with descriptive and multivariate statistics to identify potential violations of statistical assumptions. If normality is violated, then transformations or bootstrap methods will be used. For comparisons of demographic and laboratory data within- and between groups, nonparametric tests (Kruskal–Wallis) will be used. The GEE (general estimating equation) method will be applied if the data cannot be transformed. All data will be presented as mean ± standard deviation and interquartile range using absolute values and change from baseline data for all tests of structure and function unless otherwise specified.

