#### Sample size justification

Power calculations: Power analysis is based on the minimum number of subjects across the study to reach completion required for endpoint analysis of Aims 1–2. The expected dropout rate for subjects in our 2-year study is ~ 5% per 6-month period of time based on our prior natural history data in our prior studies with DLB, multiple system atrophy and Parkinson’s disease. For Aim 1, the required number needed to obtain sufficient objective pathological data (based on prior work in patients with PD and DLB) is 15 from each group (prodromal, Hoehn and Yahr stages 1, 2 and 3). Given the data in Table 1 on P-SYN values by Hoehn and Yahr stage, we estimate 5 years to move from stage 1 to 2 and 2 to 3, suggesting a ~ 16% increase in P-SYN per year. In contrast, we noted ~37% increase in P-SYN over 6 months in a prior study of dementia with Lewy bodies, consistent with an expected accelerated disease progression compared to PD. Using the data in Tables 1, 2 we expect that over 12 months we will detect a 16% increase in P-SYN across all 4 disease stages of enrollment, but with smaller absolute changes at earlier disease stages. Given the expected 10%/year dropout and 5–10% cases that are biopsy negative we require a total of 100 subjects to complete the study with > 90% power, with a 2-sided alpha of 0.05 to detect changes in P-SYN over 12 months. By increasing study duration to 18 months, we anticipate a > 90% power, with a 2-sided alpha of 0.01 to detect changes in P-SYN over 18 months in each of the 4 study subgroups (iRBD and Hoehn and Yahr stages 1–3).

**Table 1 tab1:** P-SYN quantities by H&Y staging.

Variable	H&Y Stage 1	H&Y Stage 2	H&Y Stage 3
Number	7	70	12
P-SYN (SU’s)	1.9 ± 1.3	4.6 ± 3.8	7.9 ± 5.8

**Table 2 tab2:** High sensitivity and specificity of cutaneous P-SYN detection.

Disease	Sex (M/F)	Age (± SD)	Hoehn & Yahr stage	MOCA*	P-SYN+ (#)	P-SYN+ (%)
PD	56/40	70 ± 8	2.1 ± 0.6	25.2 ± 3.7	89	92.3%
Healthy control	7/7	59.4 ± 11.1	0 ± 0	28.1 ± 1.6	4	3.3%

*MOCA, Montreal Cognitive Assessment.

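### Kruskal–Wallis is named for within-group as well as between-group laboratory comparisons; applied to the same people across visits it is invalid and strongly conservative (exploratory plasma markers only)

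*Protocol article*

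**What the plan says.** The Statistical considerations section gives laboratory data a sentence of their own, which opens "For comparisons of demographic and laboratory data within- and between groups, nonparametric tests" and names Kruskal–Wallis in parentheses as the test. The groups are defined at the start of that section as PD stages I–III and iRBD.

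The laboratory data include three plasma markers: p-tau-217, neurofilament light chain and glial fibrillary acidic protein. Under Study visits and participant data collection they come from "One 10 mL EDTA tube collected at all visits for blood-based biomarkers", and the article labels them exploratory. The same section adds that "All assessments and blood collection will be repeated once every 6 months", with genetic testing the only exception. Under Study design and cohort, "Subjects will be evaluated at baseline, 6 months, 12 months, and 18 months".

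Two methods for repeated data appear in the same paragraph as the Kruskal–Wallis sentence. Repeated measures ANCOVA comes first, with quantitative P-SYN as its primary dependent variable. GEE is to be applied only where the data cannot be transformed.

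**The concern.** Kruskal–Wallis compares independent samples. Four blood draws from one person are not independent. When one group's four visits are entered as if they were four separate groups of people, stable differences between people stay in the error term, although they cancel out of the change over time. The reference distribution is then too wide for the statistic. The test rejects far less often than its nominal level, and it loses power just where repeated sampling should help most, namely when people's values are stable relative to one another.

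At stake is how the longitudinal plasma results are reported. The study exists to describe natural history, and a non-significant within-group result could be read as a stable marker when the marker had moved.

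**Working it through.** **Is there a figure in the plan to reproduce?** No. The article states no power for the Kruskal–Wallis comparisons. The power above 90% in Sample size justification concerns P-SYN only.

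**Inputs from the article.**
- Group size: "25 subjects enrolled in each Hoehn and Yahr stage (I, II, and III), totaling 75 participants", plus 25 with iRBD, so 25 per group.
- Visits: 4.
- Dropout: about 5% per 6 months (Sample size justification). Completers per group: 25 × 0.95³ = 21.4, taken as 21.

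**Assumptions, because the article gives no values for the plasma markers.**
- Within-person correlation ρ, equal between all visits: 0.5 to 0.9.
- Linear rise over 18 months: 0 (no change), 0.5 SD and 0.8 SD, where SD is the between-person spread at one visit.
- Normal data, test level 0.05.

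**Direction, by formula.** The difference between two visit means has variance 2σ²(1 − ρ)/n. An independent-samples test works as if it were 2σ²/n. With no change, the Kruskal–Wallis statistic therefore behaves roughly like (1 − ρ) times a chi-square on 3 degrees of freedom. At ρ = 0.5 the critical value 7.815 acts like 7.815 / 0.5 = 15.63, which a chi-square on 3 degrees of freedom exceeds with probability between 0.1% and 0.2%. The nominal level is 5%.

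**Size, by simulation.** 20,000 replicates per cell, n = 21, visit shifts of 0, 1/3, 2/3 and 1 times the total rise. Both tests were run on the same data.

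| Rise over 18 months | Test | ρ = 0.5 | ρ = 0.7 | ρ = 0.8 | ρ = 0.9 |
|---|---|---|---|---|---|
| None | Kruskal–Wallis | 0.3% | <0.1% | 0.0% | 0.0% |
| None | Friedman | 4.9% | 4.8% | 4.8% | 4.7% |
| 0.5 SD | Kruskal–Wallis | 11% | 7% | 4% | 2% |
| 0.5 SD | Friedman | 37% | 58% | 77% | 98% |
| 0.8 SD | Kruskal–Wallis | 50% | 47% | 47% | 47% |
| 0.8 SD | Friedman | 79% | 95% | >99% | 100% |

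Shorter runs of the same design differ by up to about 3 percentage points. As a control, at ρ = 0 with no change both tests reject in 4.6% of trials, so the loss comes from the correlation and not from the group size.

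**All 25 followed.** At 0.5 SD, Kruskal–Wallis has 15%, 10%, 6% and 4% at the four correlations; Friedman has 43%, 67%, 85% and 99%.

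**The article's only rate of change, used as a stand-in.** For P-SYN the article expects that "over 12 months we will detect a 16% increase in P-SYN across all 4 disease stages of enrollment". Taken as 24% at 18 months, with the stage 2 mean and SD from Table 1, this is 0.24 × 4.6 / 3.8 = 0.29 SD. Within one group (n = 21 or 25, normal or log-normal data, ρ from 0.5 to 0.95), Kruskal–Wallis power is 0–3% and Friedman power is 14–95%. The article does not say that the plasma markers change at this rate.

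**The case against.** **The sentence mentions neither visits nor time.** Elsewhere the section says so explicitly when it means comparison over time. The sentence also covers demographic data, which are not compared across visits, so "within" might mean independent subgroups inside a stage, such as men and women. Kruskal–Wallis would then be valid. This stands as an ambiguity, which is why the point is conditional. The longitudinal reading remains the more natural one for markers drawn from the same people at four visits, and the article names no subgroups.

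**Methods for correlated data are already named.** A reader might infer that the plan has none; that would be wrong. They do not settle the matter, however. GEE is conditional on failed transformation, and the ANCOVA names P-SYN as its primary dependent variable, whereas laboratory data are assigned Kruskal–Wallis outright.

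**This is a condensed article.** It speaks of nonparametric tests in the plural with one in parentheses, and a fuller document may name a paired test. That is fair as to what is left out. The point here is what the article does state: one test, for both kinds of comparison.

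**The effect sizes are assumed, and small groups explain part of the low power.** Both are true. At ρ = 0.5 and a 0.5 SD rise, Friedman itself reaches only 37%.

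**Conclusion.** The point holds in conditional form. If within-group means the same people across the four visits, Kruskal–Wallis is the wrong test: its p-values are much too large, with rejection under 0.5% at a nominal 5% for correlations of 0.5 or more. Its use between groups at a single visit is sound.

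The size of the power loss depends on the assumed rise and correlation, and the article fixes neither for the plasma markers. At 0.5 SD and n = 21 it is about 11% falling to 2%, against about 37–98% for Friedman. A reader might infer that the test has almost no power whatever the change. The figures do not support that: at 0.8 SD it reaches about 47–50%, although Friedman reaches 79–100%.

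A reader might also infer that the main result is at risk. It is not. Quantitative P-SYN goes to repeated measures ANCOVA, and the affected plasma markers are exploratory. Nor would the error produce false claims of change; it runs towards missing real change. The correction is worth making because it is cheap, but the consequence is modest.

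**What to change.** State what within-group means, and split the sentence in two:
- Kruskal–Wallis for comparisons between iRBD and stages I–III at a single visit.
- For within-group change in laboratory data across visits, a method for correlated data. The GEE already named would serve if its condition of failed transformation is lifted for these data. A mixed model would also serve. Friedman (all visits) or Wilcoxon signed-rank (two visits) on completers is a simpler option. GEE and a mixed model can keep people who miss a visit; Friedman drops them, which matters with about 5% dropout per 6 months.

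The cost is one sentence in the analysis section. No extra participants, samples or visits are needed. Study blinding says that unblinding happens only at database lock, so the change can be made before then without knowledge of the results.

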#### Sample size justification

Power calculations: Power analysis is based on the minimum number of subjects across the study to reach completion required for endpoint analysis of Aims 1–2. The expected dropout rate for subjects in our 2-year study is ~ 5% per 6-month period of time based on our prior natural history data in our prior studies with DLB, multiple system atrophy and Parkinson’s disease. For Aim 1, the required number needed to obtain sufficient objective pathological data (based on prior work in patients with PD and DLB) is 15 from each group (prodromal, Hoehn and Yahr stages 1, 2 and 3). Given the data in Table 1 on P-SYN values by Hoehn and Yahr stage, we estimate 5 years to move from stage 1 to 2 and 2 to 3, suggesting a ~ 16% increase in P-SYN per year. In contrast, we noted ~37% increase in P-SYN over 6 months in a prior study of dementia with Lewy bodies, consistent with an expected accelerated disease progression compared to PD. Using the data in Tables 1, 2 we expect that over 12 months we will detect a 16% increase in P-SYN across all 4 disease stages of enrollment, but with smaller absolute changes at earlier disease stages. Given the expected 10%/year dropout and 5–10% cases that are biopsy negative we require a total of 100 subjects to complete the study with > 90% power, with a 2-sided alpha of 0.05 to detect changes in P-SYN over 12 months. By increasing study duration to 18 months, we anticipate a > 90% power, with a 2-sided alpha of 0.01 to detect changes in P-SYN over 18 months in each of the 4 study subgroups (iRBD and Hoehn and Yahr stages 1–3).

**Table 1 tab1:** P-SYN quantities by H&Y staging.

Variable	H&Y Stage 1	H&Y Stage 2	H&Y Stage 3
Number	7	70	12
P-SYN (SU’s)	1.9 ± 1.3	4.6 ± 3.8	7.9 ± 5.8

**Table 2 tab2:** High sensitivity and specificity of cutaneous P-SYN detection.

Disease	Sex (M/F)	Age (± SD)	Hoehn & Yahr stage	MOCA*	P-SYN+ (#)	P-SYN+ (%)
PD	56/40	70 ± 8	2.1 ± 0.6	25.2 ± 3.7	89	92.3%
Healthy control	7/7	59.4 ± 11.1	0 ± 0	28.1 ± 1.6	4	3.3%

*MOCA, Montreal Cognitive Assessment.

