### Statistical analysis and blinding

#### Expected outcomes

We hypothesize that cutaneous P-SYN will increase by >10% per year in patients with PD. We will confirm our ability to quantify the deposition of P-SYN in a blinded, prospective longitudinal study of clinically defined PD patients across a range of severity and measure the change in cutaneous P-SYN at 6-month intervals over an 18-month period.

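### The 16% yearly P-SYN rise behind the power claim for each subgroup averages two unequal stage steps (about 19% and 11%); it is too high for stage II and has no source for stage III or iRBD

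*Protocol article*

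**What the plan says.** In the protocol article, Sample size justification, the planning effect comes from the mean P-SYN by Hoehn and Yahr stage in Table 1 and an assumed time per stage: "we estimate 5 years to move from stage 1 to 2 and 2 to 3, suggesting a ~ 16% increase in P-SYN per year".

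The rate is then carried to every group. Over 12 months the authors expect that "we will detect a 16% increase in P-SYN across all 4 disease stages of enrollment, but with smaller absolute changes at earlier disease stages". The qualifier about absolute change shows that a constant percentage is meant.

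Two power statements follow. One is for 100 subjects, above 90%, "with a 2-sided alpha of 0.05 to detect changes in P-SYN over 12 months". The other is again above 90%, at two-sided alpha 0.01 over 18 months, separately for iRBD and for each of stages I to III.

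Under Expected outcomes the hypothesis is lower: "We hypothesize that cutaneous P-SYN will increase by >10% per year in patients with PD".

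**The concern.** A claim of power in each subgroup needs an effect size that holds in each subgroup. Table 1 gives two stage-to-stage steps, and they do not have the same percentage rate. One averaged rate may serve a single pooled statement, but applied group by group it is too high for one step and too low for the other. Table 1 also has no iRBD row and nothing beyond stage III, so two of the four groups have no step from which a rate could be taken.

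What is at stake is how a subgroup result is read. If the stage II rise is nearer 11% than 16%, the study could miss it in that subgroup more often than the stated power suggests, although 11% still satisfies the hypothesis of more than 10% per year.

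**Working it through.** **Inputs** (Table 1 and the text of Sample size justification): mean ± SD P-SYN of 1.9 ± 1.3 (stage I, n = 7), 4.6 ± 3.8 (stage II, n = 70) and 7.9 ± 5.8 (stage III, n = 12); five years per stage step; planned rate 16% per year; two-sided alpha 0.01 at 18 months.

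**1. Reproducing the 16%.** Compound rate = (ratio of means)^(1/years) − 1.
- Stage I to III over ten years: (7.9/1.9)^(1/10) − 1 = 15.3%.
- Simple mean of the two step rates in item 2: (19.3 + 11.4)/2 = 15.4%.

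So the stated figure is close to the overall average, rounded up slightly.

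**2. The two steps separately, compound.**
- Stage I to II: (4.6/1.9)^(1/5) − 1 = 19.3% per year.
- Stage II to III: (7.9/4.6)^(1/5) − 1 = 11.4% per year.

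**3. The same steps, linear.** The slopes are 2.7/5 = 0.54 and 3.3/5 = 0.66 units per year.

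| Denominator | I to II | II to III |
|---|---|---|
| Starting mean | 28.4% | 14.3% |
| Midpoint | 16.6% | 10.6% |
| End mean | 11.7% | 8.4% |

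The II to III rate is below 16% on every scale. The I to II rate is above 16% on all but the end-mean scale.

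**4. Does a uniform 16% return Table 1?** 1.9 × 1.16^5 = 4.0, against 4.6 observed. 4.6 × 1.16^5 = 9.7, against 7.9 observed.

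**5. Precision of Table 1.** Delta method on the log ratio: SE of the yearly log rate = √[(SD₁/mean₁)²/n₁ + (SD₂/mean₂)²/n₂] / 5.
- I to II: √(0.0669 + 0.0097)/5 = 0.055, giving an approximate 95% interval of 7 to 33% per year.
- II to III: √(0.0097 + 0.0449)/5 = 0.047, giving 2 to 22% per year.

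Both intervals include 16%.

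**6. Consequence for stage II power (18 months, alpha 0.01).** The stated power cannot be reproduced, because no SD of change or within-person correlation is given. As a sensitivity check, take the power at 16% as known, hold the variability fixed and shrink the effect by a ratio r:

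power = Φ[r × (2.576 + z) − 2.576], with z = 1.282 for a 90% start and 1.645 for a 95% start.

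- Compound, log scale: r = [ln(7.9/4.6)/5] / ln 1.16 = 0.1082/0.1484 = 0.729.
- Linear slope against 16% compounded over 18 months: r = (0.66 × 1.5)/(4.6 × 0.2494) = 0.863.
- Linear slope against 16% taken linearly (24% over 18 months): r = 0.99/1.104 = 0.897.

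| Stage II rate | r | 90% at 16% | 95% at 16% |
|---|---|---|---|
| 11.4% compound | 0.729 | 59% | 69% |
| Linear, against compounded 16% | 0.863 | 77% | 86% |
| Linear, against linear 16% | 0.897 | 81% | 89% |

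A paired t calculation (noncentral t) on the absolute scale gives about 56% for the first row from the 90% start. At 11.4% about twice as many stage II patients would be needed.

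**7. Stage I, same method.** At 19.3%, r = 0.1768/0.1484 = 1.191 and power rises from 90% to about 98%.

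**The case against.** The best defence is that the text offers one approximate rate for both steps together, and the ten-year average does come to about 15%. On this view a common rate is a modelling choice, and Table 1 is too small to overturn it. The two log rates differ by 0.069 with SE 0.078 (p about 0.38), so a common rate fits the data. Stage-specific rates would replace one estimate with two noisier ones. Finally, 11.4% does not conflict with the hypothesis of more than 10% per year.

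Most of this stands. The 16% is not unrelated to Table 1, and the data do not prove that the rates differ. What does not follow is the power claim group by group. Imprecise inputs do not support an unqualified figure above 90% in every subgroup, and the point estimates the authors rely on put stage II below 16% on every scale.

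A reader might go further and infer that the effect is overstated wherever P-SYN is highest, stage III included. The article does not support that. Table 1 has no step beyond stage III, so any stage III rate or power loss would be extrapolation. Nor does it show that the study as a whole is underpowered: the power statement may start well above 90%, and for stage I the same arithmetic makes 16% conservative on most scales.

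**Conclusion.** The point holds in a limited form. The 16% per year is an average of two unequal steps, about 19% and 11%, and should not be used as a uniform rate behind separate power claims.

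- **Stage II:** the effect is overstated, at 16% against 11.4% compound or 14.3% linear on the stage II mean. Power falls from 90% to about 59%, or to 77–81% on the linear reading; from 95%, to about 69%, or 86–89%.
- **Stage I:** 16% is conservative on most scales.
- **Stage III and iRBD:** 16% has no source in the article. It is unsupported, not shown to be too high.

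The power figures depend on the assumed starting power, on variability that does not change with the rate, and on reading cross-sectional stage means as a time course, as the authors do. Without the SD of change, the actual loss cannot be fixed.

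**What to change.** In Sample size justification:

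1. Describe 16% per year as the approximate average over the two stage steps.
2. Give the stage I rate (about 19%) and the stage II rate (about 11% compound, 14% linear) with their intervals.
3. Mark the rates used for stage III and iRBD as assumptions, with any basis for them.
4. Replace the claim of more than 90% power in each subgroup with power at the stage-specific rates (for example about 11% for stage II), or with the smallest yearly rise detectable in each subgroup. State the SD of change used in either case.

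The cost is a rewritten paragraph and less favourable stated power for at least stage II. Enrolment and procedures do not change.

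### The claimed >90% power at alpha 0.01 within each 25-person subgroup is not supported by the inputs the protocol states

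*Protocol article*

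**What the plan says.** The section Sample size justification makes two power claims in succession.

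- **12 months.** After allowing for dropout and biopsy-negative cases, "we require a total of 100 subjects to complete the study" with more than 90% "power, with a 2-sided alpha of 0.05 to detect changes in P-SYN over 12 months". The expected effect is "we expect that over 12 months we will detect a 16% increase in P-SYN across all 4 disease stages of enrollment".
- **18 months.** The next sentence reads "By increasing study duration to 18 months, we anticipate a" more than 90% "power, with a 2-sided alpha of 0.01 to detect changes in P-SYN over 18 months in each of the 4 study subgroups".

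The subgroups are defined under Study design and cohort: "25 subjects enrolled in each Hoehn and Yahr stage (I, II, and III), totaling 75 participants", plus "25 subjects diagnosed with iRBD, confirmed by polysomnogram (PSG), without evidence of PD".

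The stated losses are about 5% dropout per 6 months and 5–10% biopsy-negative cases. The only variability figures are the cross-sectional means and SDs in Table 1, for stages 1 to 3. Neither Table 1 nor Table 2 has an iRBD row. The section gives no test, no SD of change and no between-visit correlation.

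**The concern.** Only the second sentence mentions subgroups, so the first reads most naturally as a claim about the whole sample. On that reading, six more months is said to keep power above 90% while the sample falls to a quarter and alpha drops from 0.05 to 0.01. A longer interval enlarges the expected change by a factor of about 1.5. A quarter of the sample roughly halves the root-n factor. The signal therefore shrinks while the test becomes stricter.

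Stage-specific rates of change are a main product of this study and are meant to inform trials of disease-modifying therapy. If a subgroup of about 20 showed no clear change, a reader who trusted the stated power could conclude that P-SYN is stable in that stage, when the subgroup may simply have been too small to show the expected change.

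**Working it through.** **Reproducing the stated figure.** This is not possible. A power for change needs the SD of within-person change, which is not given. The steps below ask what value would be needed, and what the 12-month claim implies.

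**1. Evaluable numbers from the plan's own losses.**
- Whole sample at 12 months: 100 × 0.95² × (0.90 to 0.95) = 81 to 86.
- One subgroup at 12 months: 25 × 0.95² × (0.90 to 0.95) = 20.3 to 21.4.
- One subgroup at 18 months: 25 × 0.95³ × (0.90 to 0.95) = 19.3 to 20.4.

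**2. Effect.** 16% per year, taken as linear, is 24% at 18 months.

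**3. Correlation needed, from Table 1.** The test is a one-sample t-test on change, with power from the noncentral t. At n = 20 and two-sided alpha 0.01, 90% power needs a standardised change of 0.947. The SD of change can then be at most 24/0.947 = 25.3% of the mean.

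SD of change = SD × √(2(1 − r)), so r must be at least 1 − (0.253/CV)²/2. The CVs are 1.3/1.9 = 0.68, 3.8/4.6 = 0.83 and 5.8/7.9 = 0.73. The last two columns give the 95% confidence interval half-width for the 18-month change, in points of percent of the baseline mean: 2.093 × CV × √(2(1 − r))/√20.

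| Stage | r needed for 90% (n = 20) | Power, r = 0.7 | r = 0.8 | r = 0.9 | Half-width, r = 0.8 | r = 0.9 |
|---|---|---|---|---|---|---|
| 1 | 0.93 | 24% | 38% | 73% | 20 | 14 |
| 2 | 0.95 | 15% | 24% | 53% | 24 | 17 |
| 3 | 0.94 | 20% | 32% | 66% | 22 | 15 |

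With 19 evaluable the stage 2 requirement rises to 0.96. With all 25 evaluable the range is 0.91–0.94. Using all four visits or a log scale still needs 0.92–0.95. For iRBD there is nothing to compute from.

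**4. If the 12-month claim is pooled with power of 90%.**
- *Equal standardised change in every group.* With 81–86 evaluable and alpha 0.05, the standardised 12-month change is about 0.35–0.36. Multiplied by 1.5 it is 0.53–0.55, and at n = 20 and alpha 0.01 the subgroup power is 34–37%.
- *Stage-specific SDs from Table 1, one common r, iRBD assumed equal to stage 1.* The mean change is 0.16 × (1.9 + 1.9 + 4.6 + 7.9)/4 = 0.652. The implied SD of change is 0.652/0.355 = 1.84, with variance 3.37. Subtracting 0.156 for differences in mean change between groups leaves 3.22. Dividing by the mean squared SD, 12.87, gives 2(1 − r) = 0.25, so r is about 0.87. Subgroup power is then about 62%, 42% and 54% for stages 1, 2 and 3.
- Other variants widen the range. If the SD of change grows with the square root of time, power is 21–24%. With no losses and stage-specific SDs, stage 1 reaches 66%.

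**5. If the 12-month power is above 90%.** With 83 evaluable at 12 months and 20 per subgroup at 18 months, on the equal-effect basis:

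| Pooled 12-month power | Subgroup 18-month power |
|---|---|
| 95% | 45% |
| 99% | 63% |
| 99.9% | 80% |

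The subgroup claim needs a 12-month standardised change of 0.947/1.5 = 0.631, which corresponds to pooled power of about 99.99%. With that effect, 29 evaluable subjects would already give 90% power at 12 months, which does not sit with 100 being required.

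**6. If the 12-month claim is per subgroup.** With 20–21 evaluable, 90% power at alpha 0.05 needs a standardised change of 0.74–0.76. Scaled by 1.5, the 18-month power at alpha 0.01 is about 97–98%, so the two sentences agree. But an SD of change of 16/0.764 = 21% of the mean needs r of about 0.95, 0.97 and 0.96 for stages 1, 2 and 3.

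**The case against.** The strongest reply is that the text never says the 12-month claim is pooled. The same section sizes Aim 1 by group, and 100 is four times 25. Read per subgroup, the 18-month figure follows from the 12-month one. That stands as a possible reading, and it rules out calling the two sentences contradictory. It does not supply the missing input, because it relies on a still higher correlation.

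Second, Table 1 is reported in SU, while the quantitative endpoint under Biopsy analysis is µm² of P-SYN per mm² of tissue. Using the Table 1 CVs assumes that relative variability carries over. This is a fair limit on step 3, but the section itself rests its power argument on Table 1 and offers nothing else.

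Third, a full protocol or analysis plan may hold the SD of change. Its absence from an article would not matter on its own. The point here is that a specific power figure is published and that the inputs published with it do not lead to it.

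Fourth, the study is observational and no stated decision depends on subgroup power. That limits the harm to interpretation.

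Two stronger criticisms are tempting and should not be made. A reader might set "we require a total of 100 subjects to complete the study" against "A total of 100 subjects will be enrolled" and infer a conflict between completers and enrolled. The sentence begins by allowing for losses and reads naturally as 100 needed in order to run the study with that power. A reader might also infer that 16% per year is wrong, since Table 1 gives 19.3% per year from stage 1 to 2 and 11.4% from stage 2 to 3 over 5 years each. Over both steps it gives 15.3%, which agrees with an approximate single figure.

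**Conclusion.** The statement of more than 90% power at alpha 0.01 in each subgroup is not supported by what the protocol states. On Table 1 variability it needs a baseline-to-18-month correlation of about 0.93–0.96. At 0.8 and 0.9, power is well short in every stage. For iRBD the figure has no P-SYN input at all.

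A reader might infer one definite value, such as 35%, as the true subgroup power. The documents do not fix one. That value assumes that the 12-month claim is pooled, that its power is exactly 90% rather than at least 90%, and that the standardised change is equal in all groups. Under the pooled reading with power near 90%, a fair summary is roughly 35–60%, with less usual assumptions extending this to about 21–66%. Under the per-subgroup reading the stated figure follows, but only with an unstated correlation of about 0.95–0.97.

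The conclusion rests on a t-test of change, a linear 16% per year, the plan's own loss rates and, for step 3, transfer of the Table 1 CVs to the study endpoint.

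**What to change.** In Sample size justification:

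1. Remove the per-subgroup claim, or restate it with the assumed SD of change (or between-visit correlation), its source, the test and the power that results.
2. Say whether the 12-month claim refers to all subjects together or to each subgroup.
3. For each subgroup, give the expected 95% confidence interval half-width for the 18-month change over a range of correlations, as in the table above, on the scale of the study endpoint.
4. State that there are no P-SYN planning data for iRBD, so any figure for that group is an assumption.

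This changes wording only. It needs no additional participants, visits or biopsies. The cost is that the stated subgroup figure becomes less favourable unless a very high between-visit correlation can be justified.
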